### Blinding

In this single-blind study , the physical therapists are not blinded since they will treat patients according to the randomization. The researchers will be blinded to group allocation until completion of the statistical analyses. Participants will be assigned to a unique digital trial code to ensure that treatment outcome measurement and statistical analysis will be performed blind to treatment allocation. Patient information will be stored in a separate database.

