**Methods/Design:**

This paper presents the protocol of a prospective, single-blinded, multicenter cluster randomized controlled trial. In total, 200 patients with OA of the hip and/or knee will be randomly allocated into either e-Exercise or usual care (physical therapy). E-Exercise is a 12-week intervention, consisting of maximum five face-to-face physical therapy contacts supplemented with a web-based program. The web-based program contains assignments to gradually increase patients’ physical activity, strength and stability exercises and information about OA related topics. Primary outcomes are physical activity and physical functioning. Secondary outcomes are health related quality of life, self-perceived effect, pain, tiredness and self-efficacy. All measurements will be performed at baseline, 3 and 12 months after inclusion. Retrospective cost questionnaires will be sent at 3, 6, 9 and 12 months and used for the cost-effectiveness and cost-utility analysis.

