### Measurements

Three online questionnaires (0, 3 and 12 months) will be used for data collection. Participants will receive an accelerometer for the measurement of objective PA (0, 3 and 12 months). The physical therapists will measure physical functioning objectively at baseline and post-treatment (3 months). In addition, online cost questionnaires will be sent (0, 3, 6, 9 and 12 months). We offer no financial incentives to complete questionnaires or to wear accelerometers. Table 2 gives a summary of all measures that will be collected.

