**Table 2 Tab2:** **Summary of measures to be collected**

Primary outcome measures	Data collection instrument	Collection points
Physical functioning	HOOS and/or KOOS	0, 3, 12 months
	Timed “Up & Go” test	0, 3 months,
Physical activity	SQUASH	0, 3, 12 months
	ActiGraph GT3X tri-axial accelerometers	0, 3, 12 months

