#### Primary outcome measures

*Physical functioning* will be assessed subjectively with the subscale ‘function in daily living’ of the Hip OA Outcome Score (HOOS) [34] and/or the Knee Injury and OA Outcome Score (KOOS) [35], depending their affected joint. The HOOS and the KOOS assess 5 indicators: pain, symptoms, physical function, sport and recreation function and quality of life, in relation to patients’ hip or knee complaints. Each indicator is scored on a 5-point Likert scale (0 = extreme symptoms/problems; 4 = no symptoms/problems). A lower score indicates respectively more pain, symptoms, problems in physical functions, problems in sports and recreation activities and a lower quality of life. In addition, objectively physical functioning will be measured by the physical therapist with timed “Up & Go” test (TUG) [36]. In this easily administered test, the patient is requested to rise from an arm chair, walk three meters, turn, walk back again and sit down. Meanwhile, the physical therapist observes the patient and measures the time.

*Physical activity* will be measured subjectively with the SQUASH [37]. The questionnaire measures habitual PA during a normal week over the last few months. The total score is expressed as minutes per week. In addition, data can also be analysed according to whether the activity is light, moderate or vigorous. Objective PA will be measured through ActiGraph GT3X tri-axial accelerometers. Participants will be instructed to wear the monitor on a belt around their waist for five executive days [38], except during sleeping, showering or swimming. In addition, participants will be requested to fill out a short activity diary. This diary contains questions about wearing time, unusual activities and reasons for device removal. When accelerometers and diaries are returned by post, data can be downloaded, processed and subsequently analyzed. The widely accepted PA thresholds of Freedson et al. [39] will be used: 0–99 counts for sedentary activities, 100–1951 for light PA, 1952–5724 moderate PA, 5725–9498 for vigorous PA and 9499- max for very vigorous activities. The total time spent in light, moderate and vigorous PA will be summed and subsequently divided by the number of days worn to compute the daily average time spent in total activity. For analysis, data will be recorded at 1-minute intervals.

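### The plan says outcomes are measured blind to allocation, but the Timed Up & Go, a primary measure, is timed by unblinded therapists, and the primary questionnaires are self-reported by patients who know their treatment

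*Protocol article*

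**What the plan says.** The Blinding section of the protocol article makes three statements. On therapists: "the physical therapists are not blinded since they will treat patients according to the randomization". On researchers: "The researchers will be blinded to group allocation until completion of the statistical analyses". On the trial code, its purpose is "to ensure that treatment outcome measurement and statistical analysis will be performed blind to treatment allocation".

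The abstract states: "Primary outcomes are physical activity and physical functioning". Table 2 lists four instruments under these outcomes. HOOS/KOOS and the "Timed “Up & Go” test" cover functioning; SQUASH and an accelerometer cover activity. The Timed Up & Go is collected at 0 and 3 months, the other three at 0, 3 and 12 months.

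The Measurements section gives the objective measurement of functioning to the physical therapists. The Primary outcome measures section describes how the Timed Up & Go is scored: "the physical therapist observes the patient and measures the time". No other assessor is named. The Discussion counts measuring both primary outcomes subjectively and objectively, the latter by accelerometer and Timed Up & Go, among the strengths of the design.

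**The concern.** The plan claims a property for all outcome measurement that its own procedures do not give to most of the primary instruments. A trial code can hide the arm from whoever handles or analyses the data. It cannot hide it from the person holding the stopwatch, or from the patient filling in a questionnaire.

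What is at stake is how the results may be read. The Timed Up & Go is the only objective measure of functioning. A reader told that it is both objective and blind would take it as independent confirmation of the self-reported HOOS/KOOS result. If therapists in the two arms start, stop or encourage differently, part of an observed difference could come from the measurement. The Blinding section gives the reader no warning of this.

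**Working it through.** The plan states no figure on this point, so the check sets the sections side by side. A short calculation for scale follows.

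**Step 1. Do the therapists know the arm?** The Study procedure section randomizes practices and then trains therapists by arm: in e-Exercise, or in guideline-based practice. Every participating therapist in a practice therefore shares, and knows, its arm. The text says only that the physical therapist times the test. That this is the treating therapist is an inference, but little turns on it, since a participating colleague in the same practice would know the arm too. The knowledge is present at baseline as well as at 3 months.

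**Step 2. Do the patients know their treatment?** Table 1 has e-Exercise patients informed about the programme at intake, registered on the website and signing an online agreement in week 1. Usual-care patients receive ordinary physical therapy. The Blinding section does not say that patients are masked.

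**Step 3. Test the blinding claim against each primary instrument.**

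| Instrument | Who produces the value | Can the claim hold? |
|---|---|---|
| HOOS/KOOS function | patient | no |
| Timed Up & Go | physical therapist, by timing | no |
| SQUASH | patient | no |
| Accelerometer | device, then data processing | yes, for the processing |

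The statistical analysis can also be blind, as the statement about the researchers says.

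**Step 4. How much of the primary set is therapist-timed?** Three instruments at two follow-up times plus the Timed Up & Go at one give 3 × 2 + 1 = 7 contrasts between arms. One of the seven is therapist-timed.

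**Step 5. Scale, under an assumption.** If therapists shift the recorded time by the same amount in both arms, the shift cancels in the comparison. Only the difference in shift between arms, *b* in SD units, matters, and the document gives no value for it. Inputs from the Sample size section are 200 patients, 20% loss and two-sided alpha 0.05. Evaluable patients: 200 × 0.8 = 160, or 80 per arm with equal arms. Ignoring clustering and baseline adjustment, the standard error of the difference is √(2/80) = 0.158 SD. With no true effect:

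false-positive rate = Φ(*b*/0.158 − 1.96) + Φ(−*b*/0.158 − 1.96)

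| Assumed *b* (SD) | *b*/0.158 | False-positive rate |
|---|---|---|
| 0 | 0 | 5% |
| 0.05 | 0.32 | 6% |
| 0.1 | 0.63 | 10% |
| 0.2 | 1.26 | 24% |
| 0.3 | 1.90 | 48% |

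The Sample size section targets an effect of 0.2 to 0.4 in physical functioning, without saying that this refers to the Timed Up & Go. The table shows only what a bias of a given size would do. It is no evidence that such a bias exists.

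**The case against.** The strongest reply is that nothing is hidden. The study is called single-blind, the therapists are openly declared unblinded, and the text says who times the test. A trial code is a tool for data handling, so the disputed sentence can be read as describing the researchers' work only. This stands in part: it makes the fault a misleading sentence, not a concealed assessor. It does not rescue the sentence, which names outcome measurement as well as analysis and makes no exception.

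It can also be said that therapists in both arms are trained and unblinded, so any error may be equal and cancel. That stands as a limit on the claim: bias needs a difference between arms, and none is shown. The Discussion notes that e-Exercise brings therapists less reimbursement, while continued website access is offered as an incentive, so motives could run either way.

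A reader might infer more than the document supports:

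- **That the Timed Up & Go should be moved to secondary.** This would remove the only objective measure of functioning and leave that outcome on self-report, which is also unblinded. The accelerometer measures activity and cannot replace it. Demotion would not remove any bias either.
- **That the test falls at different times in the two arms**, because the Measurements section calls it post-treatment and usual care has no fixed length. The same sentence and Table 2 give 3 months without distinction by arm, and the abstract counts measurements from inclusion. The wording is loose, but the time point is fixed.
- **That the absence of a 12-month Timed Up & Go is an error.** It is an openly stated choice, and HOOS/KOOS covers functioning at 12 months.

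**Conclusion.** The blinding statement is wrong as written. It does not hold for the Timed Up & Go, which unblinded therapists time, or for HOOS/KOOS and SQUASH, which patients aware of their treatment report. Among the primary measures it can hold only for accelerometer data processing, and beyond those for the statistical analysis.

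Differential assessor bias in the 3-month Timed Up & Go, one of seven primary contrasts, is possible. Its size and direction cannot be determined from the document, and the rates in the second table rest wholly on assumed shifts. The contradiction itself needs no assumption beyond the inference that the timing therapist is one of the participating therapists. The statement should be corrected because it governs what the trial may claim for a primary measure. The point does not show that the result would be biased in favour of either arm.

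**What to change.** 1. In the Blinding section, limit the claim to accelerometer data processing and statistical analysis. State that the Timed Up & Go is timed by therapists who know the allocation and that the questionnaires are completed by patients who know their treatment. This reconciles it with the Measurements and Primary outcome measures sections.
2. In the Discussion, keep the Timed Up & Go as an objective test, but do not present it as bias-free confirmation of self-reported function.
3. As a safeguard, instruct therapists in both arms to record the follow-up time at 3 months after inclusion, whether or not treatment continues, and without sight of the baseline time. This limits expectation bias but does not mask the arm, so the statement in item 1 is still needed.
4. Keep the Timed Up & Go as a primary measure.

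The cost is a few sentences and one line in the therapists' instructions. No extra assessor, visit or patient is required.

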### Interventions

#### e-Exercise

The 3-month program e-Exercise is based on the Dutch guideline for physical therapists (10) and is a combination of (i) maximum five face-to-face sessions with a physical therapist, and (ii) a web-based PA intervention. Table 1 provides an overview of the program content of e-Exercise.

**Table 1 Tab1:** **Description e-Exercise intervention**

Intake	Physical therapist	Anamnesis and physical examination
		Assessment in- and exclusion criteria
		Providing information about osteoarthritis, e-Exercise and study
		Scheduling a follow-up appointment for week 1
	Patient	Reading patient information letter
		Signing an informed consent
		Completing baseline measurement
Start e-Exercise		
Week 1	Physical therapist	Providing information about osteoarthritis and e-Exercise
		Providing information about the 3-day baseline self-test
		Instruction of the 4 stability/mobility exercises
	Physical therapist & Patient	Registration on website to participate in e-Exercise
		Online selection of central activity and 4 stability/mobility exercises
		Providing information about the 3-day baseline self-test
		Scheduling a follow-up appointment for week 2
	Patient	Signing online treatment agreement
		Performance of a 3-day baseline test
		Performance of 4 stability/mobility exercises
Week 2	Physical therapist	Providing information about physical activity and pain
	Physical therapist & Patient	Evaluation results from the 3-day self-test
		Determining short-term goal
		Discussing the gradual increase of the selected activity
		Evaluation stability/mobility exercises
		Scheduling a follow-up appointment for week 6
	Patient	Performance of online module 1, each module consists of:
		- Gradually increase selected activity
		- Video home exercises
		- Video/text self-management themes
Week 3-5	Patient	Online modules 2-4
Week 6	Physical therapist & Patient	Evaluation online modules 1-4
		Discussing the upcoming steps and weeks
		Evaluation stability/mobility exercises
		If necessary, scheduling an additional treatment between week 7-11
		Scheduling a follow-up appointment for week 12
	Patient	Online module 5
Week 7-11	Patient	Online modules 6-10
Week 12	Physical therapist	Discussing long-term goals
		Support to maintain a physically active lifestyle
	Patient	Online module 11

#### Face-to-face sessions

During the first face-to-face session (week 1), physical therapists will provide information about OA, the importance of PA and the relation of PA with pain. Together with their physical therapist, patients choose one physical activity, for example, walking, cycling or swimming. Physical therapists select and instruct four strength & stability exercises. Patients are instructed to perform the first module of the web-based part of the intervention. In this module, the patients will be asked to determine their physical load ability based on a 3-day self-test. The second assignment is the execution of strength & stability exercises. During the second face-to-face session (week 2), patients’ physical load ability will be discussed and personal short and long-term goals will be formulated according to the principles of Goal Setting, which is based on the idea that goals can affect action [31]. The strength & stability exercises will be trained again. After the second appointment, patients are instructed to perform four online modules for the duration of four weeks. In week 6, a third face-to-face treatment takes place. Patients’ progress will be discussed, based on an online report which is automatically sent to the physical therapists. This report contains a summary of website-visits and patients’ experiences with the strength and stability exercises. After the third face-to-face treatment, patients perform another six online modules. The final face-to-face appointment will take place in week 12. In this final treatment physical therapists will support and encourage patients to maintain a physically active lifestyle. If necessary, physical therapists can plan an additional fifth session. This optional session is especially for patients who are less capable to perform unsupervised physical exercises. Physical therapists are recommended to treat patients according to the e-Exercise protocol, however, with respect to their clinical competences, physical therapist are free to deviate from the protocol.

#### Web-based PA intervention

The web-based part of e-Exercise is based on the web-based intervention Join2move [32] and consists of three topics: (i) Graded Activity; the duration of patients’ chosen physical activity (e.g. walking, cycling, swimming) will gradually be increased until patients reach their personal short-term goal. (ii) Strength & Stability; each module contains two exercises. The number of repeats will gradually increase per 4 weeks. (iii) Information; topics about OA, PA, aetiology of OA, pain-management, weight-management, motivation, medication and social influences on pain will be discussed. Automatic emails are generated if participants do not visit the website once a week.

#### Usual care

Patients in the control group will receive usual care. For the current study, usual care is defined as any treatment provided by physical therapists. Physical therapists will be encouraged to practice according to the “KNGF guideline OA Hip-Knee” [10]. According to the guideline, the physical therapy treatment comprises the same three elements as e-Exercise: (i) information, (ii) physical exercise and (iii) strength and stability exercises. Practical content considerations can be made by therapists themselves. The number of sessions will differ per patient. From the NIVEL Primary Care Database we know that the average number of physical therapy sessions in patients with OA is 17.1 [33].

### Measurements

Three online questionnaires (0, 3 and 12 months) will be used for data collection. Participants will receive an accelerometer for the measurement of objective PA (0, 3 and 12 months). The physical therapists will measure physical functioning objectively at baseline and post-treatment (3 months). In addition, online cost questionnaires will be sent (0, 3, 6, 9 and 12 months). We offer no financial incentives to complete questionnaires or to wear accelerometers. Table 2 gives a summary of all measures that will be collected.

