#### Patients

In order to include 200 participants, each physical therapist is requested to recruit about two patients. Since the study of Veenhof et al. [27] showed that recruitment of OA patients in the physical therapy practice is difficult and research has shown that different recruitment strategies do not affect treatment outcomes [28], this study uses various recruitment strategies. First, patients with hip and/or knee OA who visit a physical therapy practice will be invited to participate in the study. Second, recruitment advertisements will be placed in local newspapers. Third, information letters and flyers will be sent to general practitioners. Responders to these articles and flyers will be allocated to the nearest participating physical therapist. Eligibility criteria of patients interested in the study concern: (i) age 40–80 years, (ii) OA of the hip and/or knee according to the clinical criteria of the American College of Rheumatology (ACR) [29]. Exclusion criteria will include: (i) being on a waiting list for a hip or knee replacement surgery, (ii) being contra-indicated for PA without supervision, (iii) being sufficiently physically active according to the physical therapist, (iv) participation in a physical therapy and/or PA program in the last six months, (v) no access to internet, (vi) inability to understand the Dutch language. The diagnostic ACR clinical criteria for knee OA are: knee pain and at least three of the following six criteria: age > 50 years, morning stiffness <30 minutes, crepitation, bony tenderness, bony enlargement and no palpable warmth. Diagnostic ACR clinical criteria for hip OA are: hip pain and hip internal rotation < 15 degree and hip flexion ≤ 115 degree; or hip internal rotation ≥ 15 degree and pain on hip internal rotation and morning stiffness of the hip ≤ 60 minutes and age > 50 years [29]. Contra-indications for PA will be determined using the adapted Physical Activity Readiness Questionnaire (PAR-Q) [30]. This questionnaire is used to identify patients for whom PA is inappropriate.

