### Study procedure

Physical therapists willing to participate in the study will be screened on in- and exclusion criteria by a researcher (CK). Cluster randomization will be performed at the level of the participating physical therapy practices that will randomly be assigned to the intervention (e-Exercise) or the control group (usual care) by means of a computer-generated random sequence table. Physical therapists will receive a half day training about e-Exercise and the study procedure (intervention group) or about practicing according to the “KNGF guideline OA hip-knee” [10] and the study procedure (control group). Physical therapists will inform eligible patients about the study and screen them on in- and exclusion criteria. All suitable patients will be stimulated to contact the research team by telephone, e-mail or reply card. After an informative phone call with one of the researchers (CK or DB), interested patients will receive a letter about the trial and a request to complete an informed consent form. Patients recruited by the additional recruitment strategies (i.e. advertisements in newspapers and flyers from the general practitioner) will be informed by the researchers before they visit their physical therapist. Physical therapists in both groups will be asked to record the content of their treatment on a registration form. During the study period, both patient groups will continue their medication and usual care managed by other caregivers.

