#### Secondary outcome measures

*Information on the patients’ healthcare utilization, (unpaid) productivity losses, and sports costs due to OA* will be gathered with four retrospective 3-month cost questionnaires that cover the full 12-months of the program. Healthcare utilization due to OA comprises of visits to a physical therapist, general practitioner, massage therapist, alternative therapist, medical specialist, as well as informal care, hospital care, the use of both prescribed and over the counter drugs and medical devices. Healthcare utilization will be valued using Dutch standards costs [40]. If these are unavailable, prices reported by professional organizations will be used. Medication use will be valued using unit prices derived from the “Royal Dutch Society of Pharmacy” [41]. Unpaid productivity losses will be valued in accordance with the “Dutch Manual of Costing” [40]. Paid productivity losses comprise of both sickness absence and presenteeism (i.e. reduced productivity while at work). Sickness absence will be valued in accordance with the “Friction Cost Approach” (FCA), with a friction period of 23 weeks and an elasticity of 0.8, using age- and gender-specific price weights [40]. The FCA assumes that production losses are confined to the “friction period” (i.e. time needed to replace a sick worker) and that a 100 percent loss of labour input corresponds with an 80 percent reduction in productivity (i.e. an elasticity of 0.8) [42]. The participants’ level of presenteeism will be measured using the “World Health Organization – Work Performance Questionnaire” as well as the “Productivity and Disease Questionnaire”, and valued using age- and gender-specific price weights [40, 43–45]. The cost of the e-Exercise intervention will be estimated using a bottom-up micro-costing approach [46].

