#### Effectiveness

To determine the short (baseline-3 months) and long term (baseline −12 months) effectiveness of e-Exercise on primary and secondary outcomes, multi-level modelling of repeated measures will be performed controlling for baseline values and relevant confounders such as age, OA location and gender. With multilevel modelling of repeated measures it is possible to correct on one side for dependency of observations within subjects and, on the other side, to take into account the variation between physical therapists [50, 51]. The three-level hierarchy will exist of repeated measurements (level 1), nested within patients (level 2), nested within physical therapists (level 3).

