#### Economic evaluation

A cost-utility analysis (CUA) and a cost-effectiveness analysis (CEA) will be performed from the societal and the healthcare perspective. From the societal perspective all costs will be taken into account irrespective of who pays or benefits, whereas solely those borne by the healthcare sector will be included when the healthcare perspective is applied [40]. For the CUA and CEA, missing cost and effect data will be imputed using multiple imputation [52]. The results of the imputed datasets will be pooled using Rubin’s rules [52]. In order to account for the highly skewed nature of cost data, bias-corrected and accelerated bootstrapping with 5000 replications will be used to estimate 95% confidence intervals around the mean differences in costs between the study groups. Incremental Cost-Effectiveness Ratios (ICERs) will subsequently be calculated by dividing the differences in costs between study groups by their respective differences in QALYs for the CUA. For the CEA, ICERs will be calculated by dividing the difference in costs by the difference in PA and physical functioning. The uncertainty surrounding the ICERs will be graphically illustrated by plotting bootstrapped incremental cost-effect pairs on cost-effectiveness planes [53]. Moreover, cost-effectiveness acceptability curves (CEACs) will be constructed to provide a summary measure of the joint uncertainty of costs and effects. CEACs indicate the probability of the e-Exercise intervention being cost-effective in comparison to usual care at different willingness-to-pay values [54]. To test the robustness of the study results, several sensitivity analyses will be performed.

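### The cost questionnaire schedule contradicts itself on month 0, so it is unclear whether a baseline cost will exist, and no baseline adjustment of the cost or QALY difference is stated

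*Protocol article*

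**What the plan says.** The protocol article gives the cost questionnaire schedule in four places.

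- Measurements: "online cost questionnaires will be sent (0, 3, 6, 9 and 12 months". That is five questionnaires, the first at baseline.
- Abstract, Methods/Design: "Retrospective cost questionnaires will be sent at 3, 6, 9 and 12 months".
- Table 2, row for OA-related costs: 3, 6, 9 and 12 months. The Measurements section itself points to this table as the summary of everything collected.
- Secondary outcome measures: "four retrospective 3-month cost questionnaires that cover the full 12-months of the program".

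On analysis, Economic evaluation plans multiple imputation with Rubin's rules, and bias-corrected and accelerated bootstrapping for "95% confidence intervals around the mean differences in costs between the study groups". ICERs, cost-effectiveness planes and acceptability curves follow. No baseline cost or baseline utility is named. For the clinical outcomes, Effectiveness says that "multi-level modelling of repeated measures will be performed controlling for baseline values and relevant confounders such as age, OA location and gender".

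**The concern.** A month-0 questionnaire contributes nothing to the 12-month cost total. Its use is to supply a pre-inclusion cost, as a covariate in the cost comparison and as a predictor in the imputation. If the four-point schedule is followed, that value will not exist and cannot be recovered later. If the five-point schedule is followed, the article collects it but describes no use for it.

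The baseline value could matter because of how patients enter the trial. Study procedure states that "Cluster randomization will be performed at the level of the participating physical therapy practices". Therapists are then trained by arm, and they inform and screen patients; Blinding says that they are not blinded. The Discussion adds that e-Exercise brings them less reimbursement. Arms could therefore differ at inclusion in prior care use or work loss, by chance or through selective recruitment. An unadjusted 12-month cost difference would carry part of that imbalance into the ICERs and acceptability curves. It would also give up precision on a skewed outcome in a trial of 200 patients.

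**Working it through.** **1. Schedule.** The plan's own figure is four questionnaires. With a 3-month recall, 12 / 3 = 4, at months 3, 6, 9 and 12. This reproduces the count under Secondary outcome measures and agrees with the abstract and Table 2. The month-0 questionnaire in Measurements is a fifth, found in that one place only. It falls before the 12-month window, so the follow-up total does not change.

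**2. Precision.** The documents give no correlation r between baseline cost and 12-month cost, so r is assumed to lie between 0.2 and 0.6. Linear adjustment multiplies the variance of the cost difference by about 1 − r², and the standard error (SE) by √(1 − r²).

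| r (assumed) | 1 − r² | SE factor | SE cut by adjusting | Unadjusted SE relative to adjusted |
|---|---|---|---|---|
| 0.2 | 0.96 | 0.980 | 2% | 1 / 0.980 = 1.02 |
| 0.3 | 0.91 | 0.954 | 5% | 1 / 0.954 = 1.05 |
| 0.5 | 0.75 | 0.866 | 13% | 1 / 0.866 = 1.15 |
| 0.6 | 0.64 | 0.800 | 20% | 1 / 0.800 = 1.25 |

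**3. Chance imbalance.**

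- Completers per arm: Sample size gives 200 patients and at most 20% loss, so n = 200 × 0.80 / 2 = 80.
- Cluster size: each practice enrols one or two therapists, and "each physical therapist is requested to recruit about two patients", so m is about 2 to 4 patients per practice.
- Intracluster correlation (ICC) of cost: not given; assumed 0 to 0.1.
- Design effect: DE = 1 + (m − 1) × ICC, from 1 to 1 + 3 × 0.1 = 1.3.
- SD of the between-arm difference in mean baseline cost, in units of the patient-level SD: √(2 × DE / n), from √(2 / 80) = 0.158 to √(2.6 / 80) = 0.180.

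Only the part carried by the regression slope reaches the 12-month difference. In SD units that is r times the imbalance:

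- r = 0.2: 0.032 to 0.036 SD
- r = 0.5: 0.079 to 0.090 SD
- r = 0.6: 0.6 × 0.158 = 0.095 to 0.6 × 0.180 = 0.108 SD

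In euros, a baseline imbalance of D shifts the unadjusted difference by the slope times D, not by D. Imbalance from selective recruitment would come on top of this, and the documents give no basis for sizing it.

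**4. QALYs.** Table 2 schedules the EQ-5D at 0, 3 and 12 months, so baseline utility is collected whichever cost schedule is right. Adjusting the QALY difference does not depend on resolving month 0.

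**The case against.** A reader might infer that the cost difference is planned as an unadjusted contrast and that a baseline cost would be collected and then ignored. The documents do not support that. Economic evaluation speaks of mean differences in costs and says nothing either way about covariates. A regression-adjusted contrast is also a mean difference and can be bootstrapped. This is a condensed article, and the covariates of a cost model are commonly left to the full protocol or analysis plan. Effectiveness also extends baseline control to secondary outcomes, and Table 2 lists both costs and the EQ-5D under that heading. The separate economic section makes it doubtful that this reaches the economic analysis, but a flat statement that no adjustment is planned would go too far. This part of the objection stands, so the consequences above are conditional.

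The correlation is undocumented and could be low. The exclusion of "participation in a physical therapy and/or PA program in the last six months" and of patients on a waiting list for joint replacement narrows baseline cost variation. Part of the follow-up therapy cost is set by arm: at most five sessions against a usual-care average of 17.1. At r = 0.2 the gain in standard error is only 2%. This also stands, although the exclusions leave general practitioner and specialist visits, drugs, informal care and work loss free to vary.

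Chance imbalance across many small clusters is sampling variability, not bias, and adjustment would correct only part of any selective recruitment. Both points are fair. Finally, three places support four questionnaires and one supports five, so month 0 may be the slip. In that case keeping it adds a questionnaire.

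None of this removes the contradiction. The article states the schedule four times and disagrees with itself, which brevity does not explain.

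**Conclusion.** The contradiction is real and needs to be resolved before enrolment, because a baseline cost missed at inclusion is lost for good. It does not alter the 12-month cost total.

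On analysis, the supportable statement is that no baseline adjustment of the cost or QALY difference is stated in the economic section, while one is stated for effectiveness outcomes. If none is made, the cost of that choice is modest to moderate. Adjustment would cut the standard error of the cost difference by about 2% to 20% for r of 0.2 to 0.6; put the other way, the unadjusted standard error would be 2% to 25% larger. Chance imbalance of typical size would shift the cost difference by roughly 0.03 to 0.11 SD over the same range of r. These figures rest on an assumed correlation, an assumed cost ICC of 0 to 0.1, 80 completers per arm and a linear relation between baseline and follow-up cost. Where r is low, the stronger argument for adjustment is partial protection against imbalance from recruitment by unblinded therapists after randomisation.

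**What to change.** 1. Make the abstract, Measurements, Table 2 and Secondary outcome measures agree on month 0. Keeping it is preferable, with a stated recall of the three months before inclusion. The other four questionnaires still make up the 12-month total.
2. State that the cost difference is estimated by regression on arm and baseline cost, and the QALY difference by regression on arm and baseline EQ-5D utility, both inside the bootstrap.
3. Include month-0 cost in the imputation model.

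If the trial settles on four questionnaires, delete month 0 from Measurements. The QALY adjustment in step 2 can still be made.

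Cost: text edits and one covariate in each of two regressions. Baseline utility is already collected. If the four-point schedule was the intended one, keeping month 0 adds one short questionnaire per patient, with its respondent burden.
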